### Who will take informed consent? {26a}

Participants will be recruited from the respiratory clinics at each study site (QCH, GCUH, RDH). Before or after their appointment, families will be approached by a member of the research team to explain the study and its requirements, gauge interest, and screen for initial eligibility. Parents or carers may request a follow-up at a more convenient time or if they would like additional time to consider participation in the study.

### Additional consent provisions for collection and use of participant data and biological specimens {26b}

On the consent form, parents/guardians will provide consent for researchers to publish or present the data from this trial in a deidentified form. Additionally, if the child is withdrawn, the parent/guardian provides consent to use their data. This trial does not involve collecting biological specimens for storage.

### Interventions

#### Explanation for the choice of comparators {6b}

The therapeutic exercise group will be compared to a wait-list control group receiving usual care, which in the target patient group is currently limited to little or no exercise therapy. Its selection as a comparator is therefore justified. Children allocated to the wait-list control group will receive the exercise program at the conclusion of their 12-month follow-up period.

#### Intervention description {11a}

Children allocated to the intervention will receive the therapeutic exercise program delivered by an accredited exercise physiologist or physiotherapist. The program will include eight 60-min weekly sessions supplemented by a home-based program (two sessions per week for 8 weeks, approximately 20 min per session). This program was designed from the feasibility pilot trial [19]. Group sessions of up to six children will be conducted in community venues at different times and locations to accommodate family schedules. During group sessions, the children will participate in a warm-up and a circuit of six independent games targeting fundamental movement skills and cardiovascular fitness followed by a group game then cool down. The games alternate from higher to lower intensity and can be modified to match each child’s abilities. Children monitor their progress in a “Games Passport” and collect stickers to track their completed sessions. The home program is based on games from the group sessions. Parents receive a detailed manual describing the activities to complete in the home sessions and strategies to support and encourage children to complete the activities. Each week, the child will choose two new activities to complete with their parent at home. Parents document the number of home sessions completed each week on a chart along with the child’s perceived effort [21]. The chart is reviewed by the instructor at the next weekly session.

Prior to leading group sessions, instructors will complete 12-h of comprehensive training led by the exercise physiology and physiotherapy study investigators. Each instructor will review the intervention manual and standard operating procedures and watch videos demonstrating the setup, instructions, modifications, and basic movements for each component of the session. The training will start with the observation of the games with a focus on feedback and reflection. It will progress to leading full sessions with children, including the rehearsal of scripts developed for the home program and tracking. For quality assurance and program fidelity, heart rate data from a sensor will be collected from a sample of sessions, and instructors will complete an essential element checklist after each session. The checklist will include comments about the games completed in the session and confirmation that home session data were collected. Once the intervention has commenced, the lead exercise physiologist or physiotherapist will intermittently visit each community venue to ensure the intervention is being delivered as outlined in the study materials and training sessions.

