#### Sample size {14}

For the primary objective, the intervention effect is the difference in the percentage of children exacerbation free at 12-months follow-up. Based on the results of an RCT in which the percentage of children exacerbation free in the control group at 12 months was 18% [22], the percentage without an exacerbation over 12-months was estimated to be 20%. Based on the results of an exercise training RCT conducted on 55 adults with BE [12], we expect the therapeutic exercise program to double the percentage of children exacerbation free at 12 months follow-up from 20 to 40%. Assuming a 2-tailed alpha level of 0.05, a sample size of 79 per group (*N* = 158) will provide 80% power to detect the projected 20% group difference in the percentage of children exacerbation free at 12 months follow-up. To account for 10% attrition, a total of 174 participants will be recruited.

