#### Recruitment {15}

Participants will be recruited from the respiratory clinics at each study site (QCH, GCUH, RDH). On regularly scheduled clinic days, the clinic manager or research nurse will provide the study coordinator an appointment list of patients with a diagnosis of bronchiectasis ≥ 4 and < 13 years of age. To assess the initial eligibility, families will be asked a series of questions addressing the inclusion and exclusion criteria. Eligible and interested families will be given a participant information sheet and consent form. Following eligibility screening, the attending physician will confirm patient eligibility and provide medical clearance for exercise. To support recruitment, the exercise program will be delivered in local community halls with free parking. The exercise program will also be open to siblings and friends.

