## Statistical methods

### Statistical methods for primary and secondary outcomes {20a}

The statistical analyses will follow standard principles for RCTs using two group comparisons including all participants on an intention-to-treat basis. For the primary objective, a binary regression model with a suitably chosen link function (e.g., logistic) will be used where the target variable is whether or not an exacerbation occurred over the 12-month study period for each subject. The main covariate of interest is the treatment group (exercise vs. wait-list control). Other covariates potentially influencing the target variable such as age and sex will be considered. Therefore, the statistically determined treatment effect will be appropriately adjusted for unbalanced data with respect to the other important covariates retained in the regression model. Between-group differences in secondary outcomes—aerobic fitness, habitual PA, perceived competence, HR-QoL (PedsQL), and lung function (FEV1)—will be tested immediately post-intervention, at 6 months follow-up, and at 12 months follow-up using linear regression with treatment group (exercise vs. wait-list control) as the main effect and baseline measures of the respective outcome, along with other potential confounders (e.g., age, sex), as covariates.

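### Exercise is delivered in session groups of up to six, but the sample size and the stated regressions make no allowance for correlation within those groups

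*Protocol article*

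**What the plan says.** All references are to the protocol article.

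- **Delivery (Intervention description {11a}).** "Group sessions of up to six children will be conducted in community venues at different times and locations to accommodate family schedules". There are eight weekly sessions of 60 minutes, led by an exercise physiologist or physiotherapist, plus two home sessions of about 20 minutes each week. The instructor reviews the home chart at the weekly session.
- **Comparator (Explanation for the choice of comparators {6b}).** Controls receive usual care and are offered the programme once their 12 months are over.
- **Allocation (Sequence generation {16a}).** Children are randomized individually, 1:1, stratified by site.
- **Sample size ({14}).** "Assuming a 2-tailed alpha level of 0.05", "a sample size of 79 per group" "will provide 80% power to detect the projected 20% group difference in the percentage of children exacerbation free at 12 months follow-up". The programme is expected "to double the percentage of children exacerbation free at 12 months follow-up from 20 to 40" percent. No ICC or design effect is given. "To account for 10% attrition, a total of 174 participants will be recruited".
- **Analysis ({20a}).** "The statistical analyses will follow standard principles for RCTs using two group comparisons including all participants on an intention-to-treat basis". The primary model is a binary regression on treatment group, with covariates such as age and sex. Secondary outcomes use linear regression with the baseline value and similar covariates. No term or variance adjustment for session group, instructor or venue is named.
- **Recruitment ({15}).** "The exercise program will also be open to siblings and friends".

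**The concern.** This is a partially nested design. Exercise children spend eight weeks in small groups with a common instructor, venue and set of peers. Control children have no corresponding treatment group. Differences between instructors, in group dynamics or attendance, or in infections passed around a group, can make outcomes within a group more alike than outcomes in different groups.

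With positive correlation of this kind, the exercise arm carries less information than its head count suggests. A regression with one independent row per child then understates the standard error of the treatment effect, giving intervals that are too narrow and a type I error above the nominal 5%. Power is also below the stated figure. The mechanism is most plausible for the outcomes the sessions train directly, such as aerobic fitness and physical activity, but it applies to the primary outcome too.

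A second, separate question arises from the sentence on siblings and friends. If an enrolled wait-list child attended early, the contrast between arms would shrink. That is dilution of the effect and has nothing to do with the independence assumption.

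**Working it through.** **Inputs from Sample size {14}.** Exacerbation-free proportions 0.20 (control) and 0.40 (exercise), two-sided alpha 0.05, power 80%, 79 per group. **Input from Intervention description {11a}.** At most six children per session group. **Assumed.** ICC from 0.01 to 0.10, and *m* enrolled children per group of 6, 4 or 3. The article gives neither the ICC nor the usual group size.

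**Step 1: reproduce the plan's figure under independence.** Binomial variances are 0.20 × 0.80 = 0.16 and 0.40 × 0.60 = 0.24.

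*n* = (1.960 + 0.842)² × (0.16 + 0.24) / 0.20² = 78.49, rounded up to 79.

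Power at 79: standard error √(0.40/79) = 0.0712, and Φ(0.20/0.0712 − 1.960) = 80.3%. The stated figure is therefore the unpooled independent-observations result, with no room for a design effect. Other independent-observations formulas give 81 (arcsine), 82 (pooled) or 91 (continuity-corrected), so 79 does not conceal an allowance either.

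**Step 2: put clustering in the exercise arm only.** Design effect DE = 1 + (*m* − 1) × ICC, applied to the exercise-arm variance:

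- Power = Φ(0.20 / √[(0.16 + 0.24 × DE)/79] − 1.960)
- *n* per group for 80% power = 7.849 × (0.16 + 0.24 × DE) / 0.04
- Type I error of the unadjusted test, with equal variances under the null = 2 × [1 − Φ(1.960 / √((1 + DE)/2))]

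Worked case, *m* = 6 and ICC 0.05: DE = 1.25 and variance sum 0.16 + 0.30 = 0.46. The standard error is √(0.46/79) = 0.0763, which is √(0.46/0.40) = 1.072 times the independent value. Power = Φ(2.621 − 1.960) = 74.6%. Type I error = 2 × [1 − Φ(1.960/1.061)] = 6.5%.

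| Enrolled per group | ICC (assumed) | DE | True SE / independent SE | Type I error | Power at 79 | *n* per group for 80% |
|---|---|---|---|---|---|---|
| any | 0 | 1.00 | 1.000 | 5.0% | 80.3% | 79 |
| 6 | 0.01 | 1.05 | 1.015 | 5.3% | 79.1% | 81 |
| 6 | 0.02 | 1.10 | 1.030 | 5.6% | 77.9% | 84 |
| 6 | 0.05 | 1.25 | 1.072 | 6.5% | 74.6% | 91 |
| 6 | 0.10 | 1.50 | 1.140 | 8.0% | 69.3% | 103 |
| 4 | 0.05 | 1.15 | 1.044 | 5.9% | 76.8% | 86 |
| 4 | 0.10 | 1.30 | 1.086 | 6.8% | 73.5% | 93 |
| 3 | 0.02 | 1.04 | 1.012 | 5.2% | 79.3% | 81 |
| 3 | 0.05 | 1.10 | 1.030 | 5.6% | 77.9% | 84 |

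The type I formula does not involve the proportions, so it also applies to the linear regressions for a given ICC, with equal arms and equal variances. Power for the secondary outcomes cannot be computed because the article gives no target differences for them.

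**Step 3: dilution, as a separate illustration.** If an assumed 5% or 10% of controls obtained the full benefit, the control proportion would be 21% or 22%. Power by the unpooled formula would be about 75.5% or 70.3%. Both the rates and the full benefit are hypothetical.

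**The case against.** Several parts of the opposing case stand.

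- **The ICC is unknown.** A reader might infer that the standard errors are definitely too small. The article does not support that: at an ICC of zero nothing is understated, and at 0.01 to 0.02 the effect is small.
- **Six is a maximum.** Siblings and friends may fill places, so enrolled children per group may be fewer, and the 8.0% and 69% figures need full groups of enrolled children and an ICC of 0.10. On the other side, an instructor or venue shared by several groups could make the effective clusters larger.
- **The primary outcome may cluster weakly.** It is an antibiotic-treated exacerbation at any time in 12 months. Group contact is 8 × 60 = 480 minutes against 16 × 20 = 320 minutes at home, so 320/800 = 40% of prescribed time is outside the group. Games are adapted to the child, and instructors share training and fidelity checks. If clustering came only from variation in programme benefit, it would largely disappear under the null, and the type I inflation with it.
- **Controls are not wholly unconnected.** They share hospitals and clinics. What they lack is a treatment group, and stratifying by site does not supply or account for one.
- **Model detail may sit in a statistical analysis plan.** This is a fair point about {20a}, where the link function and covariates are left open. It does not reach {14}, where the sample size is fixed with no allowance. A later plan can also adjust for session group only if membership was recorded.

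A reader might also infer that control children will be contaminated. The article does not say so. Section {6b} places their access to the programme after 12 months, and the sentence in {15} reads most naturally as a convenience for families. It does not, however, exclude a sibling or friend who is an enrolled control.

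**Conclusion.** The point holds conditionally. The exercise arm is grouped and the control arm is not. The 79 per group is an independence figure, and the stated regressions name no allowance for grouping. If within-group correlation is positive, the plan as written overstates precision and falls short of its stated power.

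For six enrolled children per group and an ICC of 0.01 to 0.10, type I error is about 5.3% to 8.0% and power about 79% to 69%. For three per group and an ICC of 0.05, the figures are about 5.6% and 78%. The consequence therefore runs from negligible to material, and the article does not allow a narrower statement. It is a worthwhile improvement at low cost. It neither invalidates the design nor makes a case for recruiting more children.

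The sibling-and-friend sentence is a minor matter of wording: a possible source of dilution, not an established one, and with no bearing on the standard errors.

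**What to change.** 1. **Data.** Record a session-group identifier for every exercise child, with instructor and venue if easily kept.
2. **Analysis ({20a}).** For primary and secondary outcomes, specify either a partially nested model, with a random group effect in the exercise arm only, or cluster-robust standard errors with each control child as its own cluster and a small-sample correction.
3. **Sample size ({14}).** Keep enrolment at 174. Restate power over a range of ICCs and plausible numbers of enrolled children per group, as in the table above, and label the ICCs as assumptions.
4. **Recruitment ({15}), separately.** Reconcile the sentence on siblings and friends with {6b} by stating that enrolled wait-list children do not attend before their 12-month follow-up ends.

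**Cost.** One extra data field, a few sentences of text and slightly wider intervals. If the ICC is close to zero, little is lost. Under item 4, a family with an enrolled wait-list child could not bring that child along early.

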#### Criteria for discontinuing or modifying allocated interventions {11b}

There will be no special criteria for discontinuing or modifying allocated interventions.

#### Strategies to improve adherence to interventions {11c}

Adherence to the intervention will be monitored via data entered into Research Electronic Data Capture (REDCap) at the completion of each exercise session. To support adherence to the intervention, parents receive a manual that outlines the goals of the BREATH trial and includes home activity sheets. Children are given a home program tracker chart, with stickers, to display in a visible location. Similarly, children add stickers to their Games Passport at the end of each session. Instructors contact parents via text or phone call as a reminder prior to each session.

#### Relevant concomitant care permitted or prohibited during the trial {11d}

Usual concomitant care is permitted for both intervention and wait-list groups. Participation in additional research trials is prohibited during the trial.

#### Provisions of post-trial care {30}

There is no anticipated harm and compensation for trial participation.

### Outcomes {12}

Baseline data collection from parents will include demographics (date of birth, sex, parental age, parental education, household income, and family structure) and relevant medical history. Anthropometric characteristics (height, weight, body mass index (BMI), BMI *z*-score) and medical information (duration and type of cough and current medications) will be measured at each time point. Spirometry data will be extracted using the most recent data in the child’s electronic medical record.

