### Trial design {8}

The BREATH trial is designed as a randomized, controlled, multi-center, observer-blinded, parallel-group (1:1 allocation), superiority trial. Following informed consent/assent, enrolled children will complete baseline assessments (T1). Participants will then be randomized to either the therapeutic exercise program or wait-list control condition. The number of exacerbations and secondary outcomes will be assessed immediately post-intervention at 9 weeks (T2), after 6-months of follow-up (T3), and after 12 months of follow-up (T4).

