##### Lung function—spirometry

Lung function outcomes will include forced vital capacity (FVC), forced expiratory volume in 1 s (FEV1), FEV1 as a percentage of predicted valued, and the ratio of FEV1/FVC. Spirometry will be completed at routine respiratory appointments at each hospital and extracted from the medical records.

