### Data collection and management

#### Plans for assessment and collection of outcomes {18a}

Trained assessors blinded to group allocation will collect the data at each study site at each time point. All assessors will be required to meet predetermined inter- and intra-observer reliability standards for each outcome. For the measurement of physical activity (MVPA), accelerometer data will be downloaded and processed into physical activity metrics offline and subsequently imported into the REDCap database.

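### FEV1 is tested between arms at 9 weeks but taken from the latest routine clinic reading, so any child without a new reading since baseline pulls that comparison towards zero

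*Protocol article*

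**What the plan says.** Two sections of the protocol article set the source of the lung-function data. Outcomes {12} states: "Spirometry data will be extracted using the most recent data in the" child's record. The section on lung function, under the secondary outcome measures, adds: "Spirometry will be completed at routine respiratory appointments at each hospital and extracted from the medical records". Neither gives a date window or requires a reading taken after randomisation.

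Two other sections treat FEV1 as if it were measured at the trial visits. Trial design {8} places the assessment of secondary outcomes at T2 (9 weeks), T3 (6 months) and T4 (12 months). Statistical methods {20a} lists the outcomes to be compared, ending with "HR-QoL (PedsQL), and lung function (FEV1)—will be tested immediately post-intervention, at 6 months follow-up, and at 12 months follow-up using linear regression". The covariates are "baseline measures of the respective outcome, along with other potential confounders (e.g., age, sex), as covariates".

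**The concern.** The data source and the analysis times do not fit together. T2 falls about one week after an 8-week programme. If a child has had no routine spirometry since baseline, the latest record entry at T2 is the entry already used as baseline. In a baseline-adjusted regression that child's outcome equals the covariate and carries no information on treatment. Each such child moves the T2 estimate towards zero.

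Lung function has a stated secondary hypothesis. A null FEV1 result at T2 could reflect the extraction rule rather than the programme, and a reader of the results could not tell which.

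**Working it through.** **The plan's own figure.** The protocol gives no sample size or power for FEV1. Its only calculation is for the primary outcome (20% against 40% exacerbation free, two-sided 0.05, 80% power). That reproduces with unpooled variances: (1.960 + 0.842)² × (0.16 + 0.24) / 0.20² = 78.5, rounded up to 79 per group. It is used below only as the number analysed.

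**Inputs.** From the protocol: T2 at 9 weeks, T3 at 6 months (26 weeks), T4 at 12 months (52 weeks), baseline value as covariate. Assumed, because the protocol does not state it: routine spirometry every I weeks, evenly spread relative to baseline.

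**Step 1: share of values that predate baseline.** The share at time t is max(0, 1 − t/I).

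| Interval I (weeks) | T2 (t = 9) | T3 (t = 26) | T4 (t = 52) |
|---|---|---|---|
| 9 or less | 0% | 0% | 0% |
| 13 | 1 − 9/13 = 31% | 0% | 0% |
| 17 | 1 − 9/17 = 47% | 0% | 0% |
| 26 | 1 − 9/26 = 65% | 0% | 0% |
| 52 | 1 − 9/52 = 83% | 50% | 0% |

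Even spacing may be generous. Families are approached around a respiratory clinic appointment. If that visit supplies the last reading and baseline follows closely, nearly all T2 values would be carried over for any interval above 9 weeks.

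**Step 2: effect on the estimate.** If a share p of children in each arm has outcome equal to baseline, the expected treatment coefficient is (1 − p) times the true one. A simulation of the planned regression checked this: 79 per arm, assumed true effect 0.30 SD, assumed baseline correlation 0.8, 4,000 replicates.

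| Share carried over | Mean estimate (SD) | Power |
|---|---|---|
| 0% | 0.30 | 87% |
| 31% | 0.21 | 71% |
| 47% | 0.16 | 57% |
| 65% | 0.10 | 40% |
| 83% | 0.05 | 20% |

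The formula agrees: 0.30 × 0.69 = 0.21 and 0.30 × 0.35 = 0.105.

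**Step 3: equivalent loss of sample.** Convert each power to 1.96 + z(power): 3.09 at 87%, 2.53 at 71.4% and 1.70 at 39.6% (the unrounded simulated values for the second and third). The sample-size ratio is the square of the ratio to the undiluted case: (3.09/2.53)² = 1.5 at 31%, and (3.09/1.70)² = 3.3 at 65%. Repeating this with baseline correlations from 0.5 to 0.9 gives about 1.6 and 3.3 to 3.6. A fair summary is roughly 1.5 to 3.5.

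**Step 4: T4 against T3.** By the same formula, the share of T4 values that repeat the T3 reading is max(0, 1 − 26/I): 0% up to I = 26 and 50% at I = 52.

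**The case against.** **The Outcomes sentence may describe baseline only.** Read alone, it could. The lung-function section removes that reading, because it names routine appointments as the source for the outcome itself. The medical review at each time point is stated for documenting exacerbations and does not mention spirometry.

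**An article leaves windows and dates to the full protocol or SAP.** This is true, and their absence is not the point. The point is a stated rule, the most recent routine reading, applied to a stated 9-week test. A later document can add a window, but a window cannot create a 9-week reading that routine care did not produce.

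**Stronger readings a reader might infer.** Five are tempting and go beyond the document:

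- *Most T2 values will predate randomisation.* The clinic interval is not stated, and the share is zero if visits come every 9 weeks or less.
- *The whole lung-function comparison is uninterpretable.* For intervals up to 26 weeks, no T3 or T4 value predates baseline under even spacing.
- *The loss equals 2.1 to 8.4 times the sample.* That is 1/(9/13)² and 1/(9/26)², which assume unchanged residual variance. Children whose outcome equals the covariate add little residual variance, so the loss is smaller.
- *Routine spirometry contradicts blinded data collection.* The protocol says "Trained assessors blinded to group allocation will collect the data at each study site at each time point". A blinded assessor extracting a record value is compatible with that.
- *Illness-driven visits bias T3 and T4.* The lung-function section specifies routine appointments. The most-recent rule leaves acute-visit readings possible, but nothing says that they occur, and no size can be given.

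These objections limit the point to T2 and make its size conditional. They do not remove it.

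**Conclusion.** The point holds for the 9-week comparison of FEV1. The protocol's own extraction rule lets a reading taken before randomisation serve as the T2 outcome, and the between-arm estimate then shrinks by about the share of such children. That share depends on an interval the protocol does not give: 0% at 9 weeks or less, about 31% at 13 weeks and about 65% at 26 weeks, assuming evenly spread visits. The matching loss is roughly 1.5 to 3.5 times the sample after baseline adjustment, for the assumed effect and correlations.

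At T3 and T4 the readings are largely post-randomisation for intervals up to 26 weeks, although their timing is not tied to the visit. Only a secondary outcome is affected. The primary analysis and its sample size stand.

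**What to change.** Reconcile Trial design {8}, Outcomes {12}, the lung-function section and Statistical methods {20a} as follows.

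1. Drop the T2 between-arm test of FEV1, or at least do not present it as an immediate post-intervention result.
2. At T3 and T4, use only readings dated after randomisation and, at T4, after the T3 date. Record the date of every spirometry value used, and treat readings that predate randomisation as missing.
3. Analyse FEV1 % predicted, which the lung-function section already lists, because the children are growing and test dates will differ.
4. Set any date window from the clinic intervals actually found. A window of ±6 weeks spans 12 weeks. Under 26-weekly visits it would capture 12/26 = 46% of children and leave about 54% of values missing; under 13-weekly visits it would capture 12/13 = 92%.

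The cost is a change of wording, a date field, one fewer comparison and some additional missing FEV1 values. No extra procedure is needed. Measuring spirometry at the study visits would remove the mismatch altogether, but would add a procedure.
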